### 2.4. Sample Size Calculation

The minimal sample size to assure adequate power for this study was calculated based on the variation of the mean gingival index at 6 months after treatment [45]. Considering a difference of 0.3 in the gingival index value at 6 months between the test and control groups, a significant level of 5% (two-sided test) and an attrition rate of 10%, 58 subjects should be included in each group to provide a power of 80%, i.e., a total of 116 patients.

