### 2.7. Primary and Secondary Outcomes Variables

The primary outcome is the difference for gingival index at 6 months post-treatment [46,47]. Secondary outcomes include:

Difference between baseline and 3–6 months post-therapy for bleeding on probing (BOP) [48];

Mean number and percentage of participants with different BOP thresholds (e.g., BOP < 30%, BOP ≥ 30%), and gingival index thresholds (e.g., GI ≤ 1, GI ≥ 2) 3 and 6 months post therapy;

Difference between baseline and 3–6 months post-therapy for plaque score [49];

Differences between groups in occurrence of adverse events, compliance [50], and patient-reported outcomes [50];

Difference in the relative abundance of bacterial taxa in subgingival microbiota (alpha and beta diversity, Bray–Curtis distance and UniFrac).

Levels of 20 cytokines and inflammatory mediators in saliva at 3 and 6 months after therapy.

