### 2.13. Statistical Analysis

All statistical analyses will be performed in an independent and blind way to the allocated group, using SAS software (SAS Institute, Cary, NC, USA). The level of significance will be set at 5%. The data will be evaluated using intention-to-treat analysis with the last observation carried forward. To ensure comparability between groups, the characteristics of the patients at inclusion will be described for each of the two study groups. Quantitative variables will be described by the mean and standard deviation in case of normality of the distribution, or by the median and interquartile range otherwise. The normality of the distributions will be confirmed by the Shapiro–Wilk test. The qualitative variables will be described by the numbers and percentages of each variable.

The variation of the gingival index (difference between baseline and 6-month measurement) will be estimated and compared between the two groups using a constrained longitudinal data analysis (cLDA) model as proposed by Liang and Zeger [54]. In this mixed linear model, the initial and post-treatment values will be coded as dependent variables, with a restriction on a value common to both groups at inclusion in order to control for the change between groups with respect to the baseline value and to take into account all available measures [55]. The mean change at 6 months between the groups (adjusted on baseline values) will be estimated by the time x group interaction term. In case of deviation from normality, the difference between the baseline and 6 month measures will be calculated and compared between groups using a non-parametric analysis of covariance adjusted on the baseline measure [56,57]. The variation between baseline and 3–6 months for BOP, plaque score, alpha/beta diversity index and levels of inflammatory mediators will be analyzed by the cLDA method described above for the primary outcome. A stepwise logistic regression analysis will be performed to investigate the impact of predictor variables on the clinical endpoint for treatment (e.g., BOP < 10%, GI ≤ 1). Descriptive analyses will be performed for the number of adverse effects, compliance and patient related outcomes.

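### The secondary responder endpoints carry inconsistent or incomplete cut-offs, and the only inferential method named for them is a stepwise regression that does not say treatment arm is retained

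*Protocol article*

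**What the plan says.** Section 2.1.2 makes the effect of adjunctive probiotics on the extent and severity of gingivitis, at 3 and 6 months, a secondary objective. That is a between-arm question.

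Section 2.7 turns part of it into participant-level classes: "Mean number and percentage of participants with different BOP thresholds". The thresholds are given as examples: "BOP < 30%, BOP ≥ 30%), and gingival index thresholds (e.g., GI ≤ 1, GI ≥ 2) 3 and 6 months post therapy".

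Section 2.13 gives the analysis: "A stepwise logistic regression analysis will be performed to investigate the impact of predictor variables on the clinical endpoint for treatment". The endpoint is again illustrated by example, this time as "e.g., BOP < 10%, GI ≤ 1".

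Section 2.13 names no other inferential method for the dichotomised endpoints. Its descriptive analyses are for adverse effects, compliance and patient-related outcomes. The continuous outcomes are treated differently: GI, and then BOP and plaque score, are compared between arms by a constrained longitudinal (cLDA) model, with the effect read from the time-by-group term.

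**The concern.** There are three linked problems, all in what the article states.

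- **BOP cut-off.** The threshold in the outcome list is not the one in the analysis section, and no sentence connects them. As written, the listed 30% split has no matching test and the tested 10% split is not among the listed outcomes.
- **GI classes.** The two classes are not complementary for an index averaged over sites. A table built on them would leave some participants out of both rows.
- **Method.** Stepwise selection answers the question of which variables predict success. The secondary objective asks what the randomised treatment does. If arm competes with other candidates for entry, its effect estimate may be absent from the final model. If it is reported only when selected, the odds ratio tends to be exaggerated and the usual confidence interval is too optimistic, because neither allows for the selection.

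At stake is the interpretability of the responder comparison, which readers often find easier to use than a mean difference in an index.

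**Working it through.** **1. Thresholds side by side**

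| | Section 2.7 (outcomes) | Section 2.13 (analysis) |
|---|---|---|
| BOP | below 30% / 30% or more | below 10% |
| GI | 1 or less / 2 or more | 1 or less |
| Visits | 3 and 6 months | not stated for this model |
| Status | example | example |

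Only the BOP value differs. The lower GI class is the same in both places.

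**2. Can a participant fall between GI 1 and 2?** Section 2.7 counts participants, and Section 2.4 plans on a participant-level mean, since the sample size was "calculated based on the variation of the mean gingival index at 6 months after treatment". A mean over sites can take values strictly between 1 and 2. The gap would close only if the thresholds meant whole-number site scores, which does not fit a count of participants.

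**3. A plausible SD.** The article gives no SD, so 58 per group cannot be reproduced from its stated inputs alone. It can be solved for the SD it implies. Inputs from Section 2.4: difference 0.3, two-sided 5%, power 80%, 10% attrition.

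- n per group = 2 × (1.960 + 0.842)² × SD² / 0.3²
- SD 0.541: 2 × 7.85 × 0.2927 / 0.09 = 51.05, rounded up to 52
- Attrition: 52 / 0.9 = 57.8, rounded up to 58

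Any SD from 0.541 to 0.546 gives 58. I take about 0.54 as a working value, assuming it describes the spread of participant means at a visit.

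**4. Size of the gap (illustration).** With normally distributed participant means, mean m and SD s, the share strictly between 1 and 2 is Φ((2 − m)/s) − Φ((1 − m)/s). The means and the SD of 0.40 are assumptions.

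| m | s = 0.40 | s = 0.54 |
|---|---|---|
| 0.8 | 31% | 34% |
| 1.0 | 49% | 47% |
| 1.3 | 73% | 61% |
| 1.5 | 79% | 65% |

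Example: m = 0.8, s = 0.40 gives Φ(3.0) − Φ(0.5) = 0.999 − 0.691 = 0.307.

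**5. Can stepwise selection drop arm?** The text neither lists arm as a candidate nor says it is forced in. To see what follows if it is a candidate, a stepwise logistic model for GI at most 1 was simulated. Assumptions: control mean 1.3, SD 0.54, 52 per arm, six other candidates of which one is prognostic, entry and stay at 0.05, 300 runs per setting. Arm was absent from the final model in about 32% of runs with a true shift of 0.3, 78% with 0.15, and 97% with none. This shows that omission is a practical possibility under that reading. The percentages largely track the power of the responder comparison, so they do not measure damage done by the selection itself.

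**The case against.** The case against has real force on several points.

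- **Coverage by cLDA.** GI and BOP, from which the responder classes are cut, each have a baseline-adjusted between-arm estimate with no variable selection. A reader might infer that the randomised effect on the extent and severity of gingivitis could go unreported altogether. The article does not support that. Only the responder version is exposed.
- **Where the GI gap bites.** The logistic model uses GI at most 1, whose complement is complete. The gap affects the classes tabulated under Section 2.7, not that model.
- **Examples, not definitions.** All thresholds are examples, and Section 2.7 openly foresees several. Two firm definitions in conflict would be too strong a reading. Still, the examples disagree, and open thresholds allow a later choice. The blinded analysis stated in Section 2.13 limits that risk without removing it.
- **Silence about arm.** The article does not say arm is removable. Forced terms, candidate lists and entry rules are commonly left to a SAP, and one may lock arm in. The omission is therefore conditional. What the article does state is the choice of a selection procedure as the only inference for a between-arm endpoint.
- **A tempting figure.** One could argue that the planned effect would be lost in 40% to 49% of trials. A shift of 0.3/0.541 = 0.555 SD moves assumed control rates of 30%, 50% and 70% to 51%, 71% and 86%. With 52 per arm the power is about 60%, 60% and 51%. The arithmetic is sound, but the complement is simply the type II error of a two-proportion comparison. A model of similar power with arm forced in would be non-significant about as often, so the figure is not a cost of stepwise selection.

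**Conclusion.** The point holds in a limited form. The BOP example differs between the outcome and analysis sections (30% against 10%), the Section 2.7 GI classes are not exhaustive for a mean index, and the one inferential method named for the responder endpoints is poorly suited to a between-arm objective.

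The textual findings need no assumptions. The size of the GI gap, about 31% to 79%, rests on assumed normal means and SDs. The loss or selective reporting of the arm effect depends on arm being a selectable term, which the article leaves open, and no defensible size can be attached to it from the document.

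These are secondary endpoints. The primary GI analysis is not touched. The point should be corrected, but the main result does not depend on it.

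**What to change.** - Use the same BOP cut-off in Sections 2.7 and 2.13, stated as the definition and not as an example.
- Make the GI classes exhaustive, for example at most 1 against above 1, and name the 3- and 6-month visits in both sections.
- Estimate the between-arm responder effect with a pre-specified logistic model that always contains arm and the baseline value of the same index. Report the odds ratio and the risk difference with confidence intervals, whatever the p-value.
- Keep any stepwise predictor search as a separate exploratory analysis, labelled as such, with arm locked in.

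The cost is a few lines of outcome and analysis text, with no extra data, visits or participants. It should be settled before treatment codes are available to the analyst.

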## 3. Discussion

As the health and expectations of the population are improving, orthodontic treatment needs are increasing. The prevalence of malocclusions in children and adolescents varies between populations but remains high overall, estimated to range from 39 to 93% [60]. According to a previous survey in the UK, approximately one-third of children would benefit from orthodontic treatment [61,62]. Similar results have been reported in other European countries [63,64,65]. Maintaining a high standard of oral hygiene during orthodontic treatment is one of the most challenging aspects of clinical orthodontics [66]. Indeed, patients undergoing orthodontic treatments with fixed appliances typically have a higher accumulation of biofilm which exposes them to a higher risk of caries and gingivitis that can impair the course and outcome of treatment [5].

The use of probiotic microorganisms in the management of periodontal disease is a promising approach and a rapidly evolving field. A recent comprehensive review identified 36 RCTs published between 2009 and 2021 addressing this issue, with slightly under 50% focusing on the management of gingivitis [67]. Overall, the administration of probiotics, either as an adjunct to mechanical plaque control or as a single intervention, has yielded heterogeneous results. Some studies have shown a benefit of probiotic consumption in reducing the level of gingival inflammation and the amount of plaque [68,69], while others have failed to demonstrate any additional clinical benefit [70,71,72]. However, it is worth mentioning that the potential effect of probiotics seems to be more substantial among patients who cannot undergo strict mechanical plaque control or who concomitantly present an altered systemic inflammatory response. In patients with strict plaque control, the additional benefit of probiotics, if any, would be very limited and difficult to detect clinically [36,37,73]. From this point of view, the study population is clearly relevant. Adolescents with fixed orthodontic appliance present a higher risk of gingival inflammation due to the combined effect of the lack of access to oral hygiene related to orthodontic appliances, but also due to the elevation of sex steroid hormones that can generate an increased inflammatory response to plaque accumulation [74].

Some methodological choices were made for this study that should allow the provision of robust data and overcome the limitations of the few available studies on the benefit of probiotics during orthodontic treatment [38]. First, the administration of probiotics over a period of 3 months will allow sufficient time for colonization of the oral cavity by the probiotics and thus increase the chances of detecting a potential effect. Indeed, it has been observed that the effect of probiotics on the composition of the oral microbiota would not be detectable before 6 weeks of administration [33]. This could explain why previous studies have failed to demonstrate short-term efficacy of probiotics compared to placebo [42,75]. The planned microbiological analyses will verify whether the clinical outcomes are correlated with a bacterial shift. Secondly, the total duration of the study is 6 months, i.e., 3 months after the completion of the probiotics administration to allow us to evaluate the existence of any remaining effect of the probiotics after their discontinuation. Given that orthodontic treatments can last 20 months on average [76], patient compliance with daily intake of probiotic lozenges for the entire duration of the treatment is unrealistic. Third, it should be noted that at the beginning of the study, participants will benefit from a professional prophylaxis session since all orthodontic patients are expected to practice daily home oral hygiene as a standard of care. However, no further professional tooth cleaning or oral hygiene instruction will be provided during the study period to interfere as little as possible with the usual mechanical plaque control of the participants. Finally, the focus on a specific age group and a single type of probiotic could be considered a limitation to the extent to which the study results can be extrapolated. However, it should be kept in mind that children and young patients represent the vast majority of patients treated in orthodontics. Furthermore, *Lactobacillus reuteri* strains (DSM17938; ATCC PTA 5289) are well characterized in vitro and are the most frequently evaluated probiotic bacteria in oral clinical trials [13,67].

In conclusion, this study is expected to provide some reliable evidence regarding the effects of probiotics on gingival inflammation in patients undergoing treatment with fixed orthodontic appliances. This study should also provide new insight to better prevent periodontal disease and optimize orthodontic therapy.

## 4. Trial Status

This is the 1.1 version of the protocol dated 15 January 2021. Recruitment should start on January 2022, and we anticipate recruitment will end on January 2023.

## Figures and Tables

**Figure 1 pathogens-11-00112-f001:**
[figure not shown]
Experimental design of the study. Clin, clinical assessment; microb, microbiological assessment; biol, biological assessment; PROMS, patient-reported outcomes measures; hyg, hygiene; orthod, orthodontic.

**Table 1 pathogens-11-00112-t001:** Schedule of volunteers’ enrolment, interventions, and assessments according to the SPIRIT statement.

	Enrolment	Allocation	Post-Allocation		
TIMEPOINT	T-1		Intervention (T0)	3 Month Follow-Up (T1)	6 Month Follow-Up (T2)
ENROLMENT:					
Elligibility screen	X				
Informed consent	X				
Medical/dental history	X				
Allocation		X			
INTERVENTIONS:					
Orthodontic appliances			X		
Prophylaxis session			X		
Probiotic/placebo delivery			X		
ASSESSMENTS:					
Clinical		X		X	X
Microbiological		X		X	X
Biological		X		X	X
PROMS ^1^				X	
Compliance				X	

^1^ Patient-reported outcomes measures.

## Data Availability

No new data were created or analyzed in this study. Data sharing is not applicable to this article.
